#### Descriptive Statistics

Continuous data will be summarized as mean (SD) or median with IQR depending on data distribution, while categorical data will be presented as frequencies and percentages.

### Outcome Analysis

The primary outcome will be analyzed using MMRM based on the FAS. The model will include treatment group, visit, center, treatment-by-visit interaction, and baseline stratification factors (depression and physical function) as fixed effects, with the baseline CFQ-11 score a covariate. Within-participant correlations among repeated measurements will be modeled using an unstructured covariance matrix. If the model does not converge, alternative covariance structures such as first-order autoregressive or compound symmetry will be selected according to Akaike information criterion and convergence diagnostics. Restricted maximum likelihood estimation will be used. The primary contrast will be the adjusted between-group mean difference at week 8, with a 95% CI and 2-sided *P* value.

For secondary continuous outcomes, between-group differences in change from baseline will be compared at each scheduled postbaseline time point using 2-tailed Student *t* test when data are approximately normally distributed or the Wilcoxon rank-sum test when distributional assumptions are not met. This time point–specific approach is prespecified because secondary outcomes are supportive and exploratory end points, the trial is powered for the primary CFQ-11 outcome rather than for multiple longitudinal secondary scales, and the main clinical interpretation of secondary efficacy will focus on the end-of-treatment assessment. Week 4 will be used to describe early treatment response, week 8 will be defined as the main secondary efficacy time point, and weeks 20 and 32 will be used to assess durability and will be interpreted as supportive follow-up contrasts. For categorical secondary outcomes, the *χ*^2^ test or Fisher exact test will be used, as appropriate. The clinical response rate at week 8 will be compared between the groups using logistic regression adjusted for baseline CFQ-11 score, center, and baseline stratification factors. Ordinal CGI outcomes will be analyzed using proportional-odds models when the proportional-odds assumption is met; otherwise, nonparametric methods will be used. AE rates will be summarized descriptively and compared using the *χ*^2^ test or Fisher exact test when appropriate.

To address multiplicity among secondary efficacy outcomes, *P* values for the prespecified week 8 secondary efficacy outcomes will be adjusted using the Benjamini-Hochberg false discovery rate procedure at 5%. Week 4, week 20, and week 32 contrasts will not be included in this multiplicity family; these follow-up contrasts will be reported with effect estimates and 95% CIs and interpreted as exploratory supportive evidence of early response or durability rather than as confirmatory efficacy tests.

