### Randomization and Blinding

Eligible participants will be randomized in a 1:1 ratio to either the intervention group (Tuina plus UC) or the control group (UC) via a central web-based randomization system (Interactive Web Response System [IWRS]). To ensure balance between groups across the 6 centers, the minimization method will be used. Stratification factors, based on baseline data collected at the end of the run-in phase, include:

Depression severity: Hospital Anxiety and Depression Scale (HADS)-Depression score (≤10 vs ≥11).Physical function: 36-item Short Form Health Survey (SF-36) Physical Functioning subscale score (≤40 vs ≥45).

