### Statistical Analysis

The sample size was determined based on the primary outcome, namely the change in CFQ-11 total score from baseline to week 8. The variability estimate was derived from individual-level data from an investigator-initiated, single-center pilot study conducted before the current multicenter protocol was finalized. In that pilot study, the mean reduction in CFQ-11 total score was 10.29 (SD 6.02) in the Tuina group and 5.36 (SD 6.39) in the control group. Because the primary end point of the present trial is change from baseline, the SDs of the baseline-to-posttreatment change scores were used for sample size planning. These values differ from the posttreatment group-level SDs reported in the pilot study table, which described the distribution of CFQ-11 scores at the posttreatment visit rather than the distribution of change scores. The pooled SD was calculated using the following formula:

$${SD}_{pooled}=\sqrt{\frac{(n_{1}-1)\times {{SD}_{1}}^{2}+(n_{2}-1)\times {{SD}_{2}}^{2}}{n_{1}+n_{2}-2}}$$

With n_1_=n_2_=55, SD_1_=6.02, and SD_2_=6.39, the pooled SD was as follows:

$${SD}_{pooled}=\sqrt{\frac{(55-1)\times 6.02^{2}+(55-1)\times 6.39^{2}}{55+55-2}}=6.21$$

The expected between-group difference was set at 3.0 points, corresponding to the prespecified clinically useful improvement threshold for CFQ-11 [23]. This conservative choice was made because the pilot study was single-center and relatively small, and pilot-based treatment effect estimates may be unstable or overestimate the effect expected in a larger multicenter trial. Using the MCID as the target effect ensures that the trial is powered to detect a clinically meaningful difference. To detect a 3.0-point between-group difference with a pooled SD of 6.21, 90% power, and a 2-sided significance level of 0.05, 92 participants per group are required. Allowing for a 20% dropout rate, the target sample size is 115 participants per group, for a total of 230 participants. The calculation was performed using PASS software.

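### Optional precision gain: the primary MMRM uses baseline depression and physical function only as two-level flags, although the full scores are collected before randomisation

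*Protocol article*

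**What the plan says.** The Outcome Analysis section lists the terms of the primary MMRM: treatment group, visit, center, treatment-by-visit, and "baseline stratification factors (depression and physical function) as fixed effects, with the baseline CFQ-11 score a covariate". The covariance is unstructured, estimation is by REML, and the primary contrast is the adjusted difference at week 8. Treatment-by-visit is the only interaction listed. The logistic model for week 8 response adjusts for baseline CFQ-11, center and the same stratification factors.

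Randomization and Blinding defines the factors as cuts. The depression factor is "Hospital Anxiety and Depression Scale (HADS)-Depression score (≤10 vs ≥11", and the physical function factor is SF-36 PF at 40 or below versus 45 or above.

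Table 1 schedules HADS and SF-36 PF at run-in and at week 0. Allocation Concealment has the assignment released only after baseline assessments are complete. HADS-D runs from 0 to 21 (Mental Health Status). PF runs from 0 to 100 in steps of 5, so it has 21 possible values (Quality of Life).

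On sample size, Statistical Analysis states that "the SDs of the baseline-to-posttreatment change scores were used for sample size planning".

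**The concern.** Minimisation needs both scores in every randomised patient, so the information is already in hand. Splitting a score in two treats all patients on one side of the cut as alike. Whatever the score predicts within each side stays in the residual and widens the interval for the treatment difference. Adjusting for the minimisation factors is right, but it does not prevent also using the scores behind them.

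A smaller point concerns baseline CFQ-11. As listed, it enters as one covariate with no visit interaction, which implies one slope for weeks 4, 8, 20 and 32. If the relation to baseline weakens over time, a common slope fits some visits less well. Durability to week 32 is a secondary objective, so those later estimates would carry avoidable noise.

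Only precision is at stake, not validity.

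**Working it through.** **1. The plan's own figure.** The inputs are in Statistical Analysis: "To detect a 3.0-point between-group difference with a pooled SD of 6.21, 90% power, and a 2-sided significance level of 0.05". Pooled SD = √((6.02² + 6.39²)/2) = 6.208, which rounds to 6.21. With the noncentral t distribution, power is 0.8999 at 91 per group and 0.9031 at 92, so 92 is reproduced. Then 92/0.8 = 115 per group, 230 in total. No covariate adjustment is credited in this calculation.

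**2. What a cut keeps.** For a normal score with a linear effect, a cut with a share p beyond it keeps φ(z)²/(p(1−p)) of the score's R²:

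- p = 0.5: 0.3989²/0.25 = 0.64
- p = 0.3: 0.3477²/0.21 = 0.58
- p = 0.2: 0.2800²/0.16 = 0.49

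**3. Effect on week 8 residual variance.** The article gives no prognostic correlations, so the values here are assumptions: each score has partial correlation r with week 8 change after baseline CFQ-11, 30% of patients lie beyond each cut, and the scores are oriented so that both point towards worse health. With correlation ρ between the scores and ρ_f between the flags:

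- R² from scores = 2r²/(1+ρ)
- R² from flags = 2r² × 0.576/(1+ρ_f)
- variance ratio = (1 − R² scores)/(1 − R² flags)

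| r | ρ | ρ_f | R² scores | R² flags | Ratio | Variance saved |
|---|---|---|---|---|---|---|
| 0.2 | 0 | 0 | 0.080 | 0.046 | 0.964 | 3.6% |
| 0.2 | 0.3 | 0.18 | 0.062 | 0.039 | 0.977 | 2.3% |
| 0.2 | 0.5 | 0.32 | 0.053 | 0.035 | 0.981 | 1.9% |
| 0.1 | 0 | 0 | 0.020 | 0.012 | 0.991 | 0.9% |
| 0.3 | 0 | 0 | 0.180 | 0.104 | 0.915 | 8.5% |

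Simulated four-visit MMRMs (230 patients, 20% dropout, unstructured covariance) gave a similar size: about 2% lower model-based variance at week 8 for weak prognostic strength and about 7% for moderate. Mean estimates stayed close to the simulated 3-point effect under every model.

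**4. Power.** Adjusting for baseline CFQ-11 already changes the starting point. If baseline and week 8 variances are equal and correlate at r_b (assumed), the adjusted variance is (1+r_b)/2 of the change-score variance:

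- r_b = 0.5: SD = 6.21 × √0.75 = 5.38, power at 92 per group 96.4%
- r_b = 0.6: SD = 6.21 × √0.80 = 5.55, power 95.4%

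A further 3.6% cut in variance gives 96.9% and 96.0%, a gain of about 0.5 to 0.6 points.

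**5. Baseline slope by visit.** If a common slope b is fitted where visit j has slope β_j, the residual variance at that visit grows by the fraction SD_b²(β_j − b)²/σ². Take assumed slopes of 0.7, 0.5, 0.4 and 0.3, baseline SD 4.5, residual SD 5.4 and equal correlation between visits, so b = 0.475:

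- Week 8: (20.25/29.16) × 0.025² = 0.0004, or 0.04%
- Week 32: (20.25/29.16) × 0.175² = 0.021, or 2.1%

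In the simulations, freeing the slope lowered week 8 variance by nothing when slopes were equal, by under 0.5% for a smooth decline with week 8 near the average, and by 3% to 14% when slopes differed markedly between visits.

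**The case against.** The strongest reply is that nothing here is wrong. The model adjusts for center and both minimisation factors, carries baseline CFQ-11 as a continuous covariate, and uses an unstructured covariance with REML. Using the factors as randomised is common and defensible. That stands, and it is why the point is offered as an improvement.

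The size rests on assumption. No prognostic correlation appears in the article, and depression and physical function are unlikely to be independent in one illness, so about 2% is as plausible as 3.6%. The share kept by a cut also assumes normal scores and a linear effect. All of this stands.

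The single baseline slope is read from an omitted term; the article does not state that the slope is constant. A separate analysis plan could add the interaction. This also stands, and it keeps that half of the point secondary.

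A flag and its score overlap heavily (correlation √0.58 = 0.76 under the normal model). That blurs their own coefficients but does not harm the treatment contrast.

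A reader might infer that the trial is underpowered, or that this change would lift power from 90% to 91%. The article does not support either. The 90% is computed from the raw change-score SD, whereas the planned model already adjusts for baseline CFQ-11, so its power would probably start above 90%.

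**Conclusion.** The point holds as a small, free gain in precision. The primary MMRM, as listed, uses two-level versions of two scores that are fully recorded before randomisation. Under the stated assumptions (normal scores, linear effects, partial correlation 0.2, 30% beyond each cut), adding the scores lowers week 8 residual variance by about 2% to 3.6%. For partial correlations of 0.1 to 0.3 with independent scores, the range is about 1% to 8.5%. The gain in power is likely to be under one percentage point at r = 0.2.

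It would be wrong to conclude that the primary analysis is biased or invalid: the simulations show no bias, and the adjustment matches the randomisation. The visit-specific slope barely matters for the week 8 contrast if slopes decline smoothly. Its value lies in the week 20 and week 32 estimates, and only if the baseline relation does change over time.

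**What to change.** In Outcome Analysis, keep center and the two minimisation factors in the primary MMRM and add baseline HADS-D and SF-36 PF as continuous covariates. Make the same addition to the logistic model for week 8 response. As a secondary change, add a baseline CFQ-11-by-visit interaction to the MMRM. Fix the wording before unmasking.

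The cost is about five extra parameters in the MMRM (two score slopes and three interaction terms for four post-baseline visits) against 230 planned patients. No new data are needed, and the primary contrast and the sample size are unchanged.

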**Methods:**

This prospective, multicenter, randomized, open-label, assessor-blinded, parallel-group clinical trial will be conducted at 6 hospitals in China. The study consists of 3 phases: a 1-week run-in period, an 8-week treatment period, and a 24-week follow-up period. A total of 230 eligible participants diagnosed with CFS (Centers for Disease Control and Prevention 1994 criteria) will be recruited and randomly allocated (1:1) to receive either Tuina therapy plus UC (intervention group) or UC alone (control group). The intervention group will undergo 24 sessions of a standardized Tuina protocol over 8 weeks (3 sessions/week). Follow-up assessments will be conducted at weeks 4, 8, 20, and 32. The primary outcome is the change in fatigue severity measured by the 11-item Chalder Fatigue Questionnaire from baseline to week 8. Secondary outcomes include clinical response rate, sleep quality, anxiety, depression, quality of life, adverse events, and clinical global impression. Efficacy analysis will be performed using a mixed-effects model for repeated measures in the modified intention-to-treat population. Secondary outcomes will be analyzed as exploratory supportive end points using appropriate parametric or nonparametric tests based on data distribution, with week 8 defined as the main secondary time point and later follow-up visits interpreted as durability contrasts. Missing outcome data will be handled primarily through likelihood-based mixed-model estimation under a missing-at-random assumption, with multiple imputation and per-protocol analyses used as sensitivity analyses.

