### Missing Data

All missing data will be documented with reasons whenever possible and summarized by group and visit. No last-observation-carried-forward approach will be used. The primary MMRM analysis handles missing repeated outcome data through likelihood-based estimation under the missing-at-random assumption, using all available observed data. Multiple imputation by chained equations will be performed as a sensitivity analysis for the primary outcome and key secondary continuous outcomes when postbaseline data are missing. The imputation model will include treatment group, center, baseline stratification factors, baseline outcome values, observed postbaseline outcomes, demographic variables, and relevant UC or concomitant-treatment variables. At least 50 imputed datasets will be generated, and estimates will be combined using Rubin rules [28-30]. For the clinical response rate, response status will be derived from imputed CFQ-11 values in the MI sensitivity analysis; an additional conservative sensitivity analysis will classify participants with missing week 8 CFQ-11 data as nonresponders. If overall missingness exceeds 20% or differs between groups by more than 10 percentage points, additional sensitivity analyses using delta-adjusted pattern-mixture methods will be considered to assess departures from the missing-at-random assumption. Additionally, the robustness of the primary outcome will be assessed using the PPS population as a sensitivity analysis.

All statistical analyses will be performed using SAS version 9.4 (SAS Institute). Statistical significance is defined as a 2-sided *P*<.05.

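### Continuous secondary outcomes are tested without the baseline, center and minimization covariates that the plan uses elsewhere, which costs precision and makes some tests conservative

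*Protocol article*

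**What the plan says.** The Outcome Analysis section sets three levels of analysis.

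- **Primary outcome.** CFQ-11 is analysed by an MMRM with treatment, visit, treatment-by-visit, center, the two stratification factors and baseline CFQ-11.
- **Responder rate and CGI.** The week 8 responder rate has a logistic model adjusted for baseline CFQ-11, center and the stratification factors. CGI has a proportional-odds model.
- **Continuous secondary outcomes.** Here "between-group differences in change from baseline will be compared at each scheduled postbaseline time point using 2-tailed Student" t test, or the Wilcoxon rank-sum test if the distribution is unsuitable. No covariates are named. The reasons given are that these outcomes are exploratory, that the trial is powered on CFQ-11 and that interpretation centers on week 8.

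The week 8 secondary P values then enter a Benjamini-Hochberg procedure at 5%.

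The Randomization and Blinding section uses minimization across 6 centers. It introduces two further factors with the words "Stratification factors, based on baseline data collected at the end of the run-in phase, include" and lists HADS-Depression (10 or below against 11 or above) and SF-36 Physical Functioning (40 or below against 45 or above). Both scales are also secondary outcomes.

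On missing data, the abstract states without restriction: "Missing outcome data will be handled primarily through likelihood-based mixed-model estimation under a missing-at-random assumption". The Missing Data section ties the likelihood method to the primary MMRM and adds: "Multiple imputation by chained equations will be performed as a sensitivity analysis for the primary outcome and key secondary continuous outcomes". It does not say which outcomes are key.

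**The concern.** The article accepts covariate adjustment for the primary outcome and for one secondary outcome, then drops it for the six continuous scales. Its reasons explain why one visit is emphasized. They do not explain why the baseline value, center and minimization factors are left out. A trial that was not powered for these scales has more reason to use the more precise method.

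Three things follow. Precision is lost on every continuous secondary outcome. Where the outcome scale is itself a minimization factor, the usual standard error ignores the balance that the allocation creates and is too large. And a test at one visit makes no use of week 4 data from someone who misses week 8. The week 8 P values will be read inferentially because they feed a false discovery rate procedure.

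**Working it through.** **1. The plan's own figure.** The pooled SD is √[(54 × 6.02² + 54 × 6.39²)/108] = 6.21. The plan then has "To detect a 3.0-point between-group difference with a pooled SD of 6.21", with "90% power, and a 2-sided significance level of 0.05, 92 participants per group are required". The noncentral t calculation gives power 0.8999 at 91 per group and 0.903 at 92, so 92 is right. 92/0.8 = 115 per group and 230 in total, as stated. The sample size concerns CFQ-11 only and is not in question.

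**2. Precision lost by not adjusting for baseline.** Assume equal variance σ² at baseline and follow-up, with correlation ρ. The article gives no ρ for these scales, so a range is shown.

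- Variance of change: 2σ²(1 − ρ)
- Residual variance after baseline adjustment: σ²(1 − ρ²)
- Ratio: (1 + ρ)/2

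| ρ | Variance ratio | Adjusted n per arm equal to 92 unadjusted | Change-score SE / adjusted SE | Adjusted power where unadjusted power is 80% |
|---|---|---|---|---|
| 0.3 | 0.65 | 60 | 1.24 | 93.5% |
| 0.5 | 0.75 | 69 | 1.15 | 90% |
| 0.7 | 0.85 | 78 | 1.08 | 86% |
| 0.8 | 0.90 | 83 | 1.05 | 84% |

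The loss is equivalent to discarding 35% down to 10% of the sample. It is present at any ρ below 1.

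**3. Size of the test for HADS-D and SF-36 PF.** Let a fraction p of participants fall on one side of the cut-point. For a normal baseline, the cut explains a share f = φ(z_p)²/[p(1 − p)] of the baseline variance: 0.637 at a 50/50 split, 0.490 at 20/80 and 0.342 at 10/90. With balance on the cut, the true variance of the change-score difference is the fraction k = 1 − (1 − ρ)f/2 of what the t test assumes. The actual size is then 2[1 − Φ(1.96/√k)].

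| Split | ρ = 0.4 | ρ = 0.6 |
|---|---|---|
| 50/50 | 2.9% | 3.6% |
| 20/80 | 3.4% | 3.9% |
| 10/90 | 3.9% | 4.2% |

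Over ρ from 0.3 to 0.8, the extremes are 2.6% (50/50, ρ = 0.3) and 4.6% (10/90, ρ = 0.8). These figures assume exact balance among those analysed.

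A simulation of 230 participants used minimization on center and one baseline factor, 20% missing completely at random, and assumed center effects from −0.5 to +0.5 SD (3,000 replicates). At ρ = 0.3, 0.5 and 0.7 the results were:

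- Type I error: 2.6%, 3.5% and 3.5% unadjusted; 4.4%, 5.5% and 4.8% adjusted.
- Power for a 0.45 SD effect: 0.71, 0.84 and 0.97 unadjusted; 0.87, 0.94 and 0.99 adjusted.

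**4. Missing data.** The plan has "Allowing for a 20% dropout rate, the target sample size is 115 participants per group, for a total of 230 participants". If the allowance were used up, 0.20 × 230 = 46 participants would be absent from each week 8 test. As an illustration, suppose that about 20% drop out depending on the week 4 value and that week 4 and week 8 correlate at 0.6. Analysing only those observed then gives a bias of about 0 if the mechanism is the same in both arms, 0.10 SD if it acts in one arm only, and 0.21 SD if it runs in opposite directions. A mixed model using the week 4 data is valid under that assumption.

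**The case against.** The best defence is that these outcomes are labelled exploratory, the method is openly prespecified with reasons, and a change-score comparison in a randomized trial with complete data is unbiased. All of that stands. It limits the weight of the point but does not explain why the covariates are omitted.

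Some stronger readings are tempting and are not supported:

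- **That the analysis contradicts the Missing Data section.** It does not. That section confines the likelihood method to the primary MMRM. The mismatch is only with one general sentence in the abstract, and the sentence before it already assigns secondary outcomes to simple two-group tests.
- **That dropout bias is left unhandled even under missing at random.** Multiple imputation is planned for key secondary outcomes, with observed postbaseline values in the imputation model. The fair criticism is that it is a sensitivity analysis only and that the key outcomes are not named.
- **That all secondary outcomes are affected.** The responder rate and CGI have their own models.
- **That the Wilcoxon branch cannot deliver the promised estimates and intervals.** The article promises effect estimates with 95% CIs for weeks 4, 20 and 32, not mean differences. A Hodges-Lehmann shift with its CI would meet that promise, and the choice of estimator can be left to the SAP.
- **That false positives are at risk.** The distortion shown from ignoring the minimization factors is in the conservative direction.
- **That an MMRM would recover all 46 participants.** The 20% is a planning allowance, and people with no postbaseline data add essentially nothing to the week 8 contrast. Those seen only at week 4 add part of their information.

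It is also fair that the size of the effect depends on a correlation and on cut-point positions that the article does not give. At ρ = 0.8 the variance saving is only 10%.

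**Conclusion.** The point holds as a moderate one that should be fixed. The planned tests for the continuous secondary outcomes are unadjusted and in effect use only participants observed at each visit, while the primary and responder analyses adjust. Baseline adjustment would have 65% to 90% of the change-score variance, assuming equal variances and ρ between 0.3 and 0.8. For HADS-D and SF-36 PF, the unadjusted test is conservative at roughly 3% to 4% instead of 5%, depending on ρ and where the cut-points fall. The main analysis of these outcomes has no missing-at-random handling beyond sensitivity imputation for unnamed key outcomes, and the abstract's general sentence fits only the primary outcome. The primary analysis, the CFQ-11 follow-up contrasts from its MMRM, and the sample size are unaffected.

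**What to change.** Analyse each continuous secondary outcome with the MMRM already specified for CFQ-11: that outcome's own baseline value, center, the two stratification factors, treatment, visit and treatment-by-visit. Report adjusted differences with 95% CIs at weeks 4, 8, 20 and 32, and feed the week 8 P values into Benjamini-Hochberg. Keep the rank tests as a sensitivity analysis. Name the key outcomes for multiple imputation. Reword the abstract sentence so that it matches the main text; once the MMRM covers the continuous secondary outcomes, it can include them too.

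The cost is wording in the analysis plan and abstract, plus reuse of the primary model code. The Table 1 schedule already collects these scales at baseline and all four later visits, so no new data are needed.

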### Data Analysis Plan

#### Analysis Populations

The primary efficacy analysis will be based on the modified intention-to-treat (mITT) population, operationalized as the full analysis set (FAS). The FAS will include all randomized participants with valid baseline CFQ-11 data who either receive at least 1 component of the allocated study management after randomization or provide at least 1 postbaseline CFQ-11 assessment. Study management refers to Tuina and/or usual care in the intervention group and usual care in the control group. Participants in the FAS will be analyzed according to their randomized allocation, irrespective of adherence, treatment discontinuation, number of completed sessions, protocol deviations, or concomitant care.

Participants who do not initiate any allocated postrandomization study management but provide valid postbaseline CFQ-11 data will remain in the FAS and will be analyzed according to randomized allocation. Postrandomization exclusions from the FAS will be limited to participants who withdraw consent for use of all data, have no valid baseline CFQ-11 data, are found after randomization to have a major eligibility error, or withdraw immediately after randomization before any study management and provide no postbaseline primary outcome data. All such exclusions will be documented before database lock and summarized in the participant flow diagram.

The per-protocol set (PPS) will include participants who complete at least 80% of the assigned intervention requirements, have week 8 primary outcome data, and have no major protocol violations. The safety set (SS) will include all randomized participants who receive at least 1 component of the allocated intervention or usual care and will be analyzed according to treatment actually received.

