## Discussion

### Principal Findings

This protocol describes a multicenter randomized trial designed to test the hypothesis that 8 weeks of standardized Tuina therapy plus UC will produce a clinically meaningful reduction in fatigue severity compared with UC alone among patients with CFS. We also hypothesize that Tuina will increase the clinical response rate, improve sleep, mood symptoms, physical function, bodily pain, and health-related quality of life, and show acceptable safety. The 24-week posttreatment follow-up will allow the assessment of whether any treatment benefits are sustained beyond the active intervention period.

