### Future Directions and Dissemination

If Tuina is shown to be effective and safe, it could serve as an adjunctive nonpharmacological option for CFS management. The standardized protocol may support practitioner training and facilitate implementation in clinical settings. Future research should examine pragmatic delivery models, cost-effectiveness, objective activity or physiological outcomes, mechanisms of action, and effectiveness across alternative CFS/ME diagnostic criteria. Trial findings will be disseminated through peer-reviewed publications, conference presentations, trial registry updates, and sharing of the standardized Tuina protocol where appropriate.

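### Safety is an objective and a hypothesis, but the only between-arm adverse event analysis named is a significance test with no effect estimate or confidence interval, and it cannot support that hypothesis

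*Protocol article*

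**What the plan says.** The Abstract's objective covers efficacy and safety together, and the Objective section of the Methods lists safety among the secondary objectives. Under Principal Findings, the hypothesis is that Tuina will raise the response rate, "improve sleep, mood symptoms, physical function, bodily pain, and health-related quality of life, and show acceptable safety". Future Directions and Dissemination makes later use conditional: "If Tuina is shown to be effective and safe, it could serve as an adjunctive nonpharmacological option for CFS management".

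The analysis is one sentence in Outcome Analysis: "AE rates will be summarized descriptively and compared using the *χ*^2^ test or Fisher exact test when appropriate". The closing statement of the Missing Data section applies to all analyses: "Statistical significance is defined as a 2-sided *P*<.05". Safety and Adverse Event Reporting adds that the number and type of AEs will be calculated. It names the reactions to watch for in the Tuina arm (bruising, persistent local pain, skin abrasion, fainting) and sets a 24-hour SAE reporting rule.

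The safety population is given in Analysis Populations: "The safety set (SS) will include all randomized participants who receive at least 1 component of the allocated intervention or usual care", analyzed by treatment actually received. The article states no expected AE rate, no margin and no definition of acceptable safety.

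**The concern.** The stated hypothesis and the stated test do not match. A chi-square or Fisher test takes equal AE risk as its null hypothesis. Rejection is evidence of a difference. Failure to reject says only that the data are compatible with no difference, and they may be equally compatible with a material excess. To support a statement that safety is acceptable, the reader needs the largest excess risk that the data do not exclude, which is a confidence limit.

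The article does name intervals elsewhere. The primary week 8 contrast gets a 95% CI, and the week 4, 20 and 32 contrasts get effect estimates with 95% CIs and an explicit note that they are not confirmatory. The AE comparison gets no interval and no such note. The trial was sized on the CFQ-11 alone, so the AE test has whatever power the event rate happens to give it. At stake is how the safety half of the conclusion is worded if few events occur and P exceeds .05.

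**Working it through.** **1. The article's own figure.** The article states no AE power or margin, so the only figure to reproduce is the sample size.
- Inputs (Statistical Analysis): difference 3.0, SDs 6.02 and 6.39, power 90%, 2-sided .05, dropout 20%.
- Pooled SD = √[(6.02² + 6.39²)/2] = 6.21.
- The two-sample t-test solution is 91.02, rounded up to 92 per arm. 92/0.8 = 115 per arm.
- The stated 92, 115 and 230 are reproduced. None of these inputs concerns AEs.

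**2. Power of the AE test.**
- Arm size: 115, if everyone randomized enters the safety set. This is the planned maximum.
- Control AE rate p: *assumed*, because the article gives none. The Tuina rate is taken as 2p.
- For i and j participants with an event in two arms of n, the uncorrected chi-square statistic is X² = [(i − j)/n]² / [p̄(1 − p̄)·2/n], with p̄ = (i + j)/(2n). It is significant if X² > 3.84. The Fisher test is significant if its exact 2-sided P < .05.
- Power = the sum over all (i, j) of Bin(i; n, p) × Bin(j; n, 2p) × 1[significant]. Miss probability = 1 − power.

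| Assumed rates (UC vs Tuina) | Missed, chi-square | Missed, Fisher |
|---|---|---|
| 2% vs 4% | 88% | 94% |
| 5% vs 10% | 69% | 79% |
| 10% vs 20% | 43% | 50% |
| 15% vs 30% | 21% | 26% |
| 20% vs 40% | 8% | 11% |

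With 92 per arm, the miss probabilities are 75%/83% at 5% vs 10% and 52%/60% at 10% vs 20%. By the normal approximation, 80% power for 5% vs 10% would take about 435 per arm.

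**3. What an interval adds: an illustrative result.** Suppose 12/115 participants (10.4%) have the event on Tuina and 6/115 (5.2%) on usual care.
- p̄ = 18/230 = 0.0783. X² = (6/115)² / (0.0783 × 0.9217 × 2/115) = 2.17, so P = .14. Fisher P = .22.
- Wilson 95% limits: Tuina 6.1% to 17.4%, usual care 2.4% to 10.9%.
- Newcombe lower limit: 5.2 − √[(10.4 − 6.1)² + (10.9 − 5.2)²] = −2.0 points.
- Newcombe upper limit: 5.2 + √[(17.4 − 10.4)² + (5.2 − 2.4)²] = +12.7 points (both limits from unrounded inputs).

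The P value alone reads as no difference. The interval shows that an excess of up to 12.7 points is not excluded.

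**4. No events at all.** With 0/115 SAEs on Tuina, the exact 2-sided 95% upper limit is 1 − 0.025^(1/115) = 3.2%.

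**The case against.** The strongest reply is that the article nowhere makes the P value a safety decision rule. Acceptable safety is a hypothesis, the later statement about use is conditional, and the test stands beside descriptive counts, monitoring of named reactions and SAE reporting. This is correct. A reader might infer that the trial intends to declare Tuina safe on P>.05, but the text does not say so.

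A second reply concerns size. A reader might take a miss rate of roughly 70–80% as a feature of the design. It is not: that range belongs to an assumed 5% vs 10%. The AE definition covers any untoward occurrence whatever its cause, with recording scheduled to week 32, so the any-AE rate could be much higher. At 20% vs 40% the test misses a doubling only 8–11% of the time. Nor is a non-significant result always the expected one under a doubling: at 10% vs 20% chi-square power is 57%. The cited review's report of few adverse reactions to massage does not fix the rate for this broader endpoint.

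Third, limited AE power is usual in a trial sized for efficacy, AE reporting detail often sits in an analysis plan, and the week 8 secondary outcomes are not explicitly promised intervals either. All of that stands, and it lowers the severity. It does not remove the point, which concerns the method the article states and the hypothesis it states: the first cannot support the second.

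**Conclusion.** The point holds at minor severity. The only between-arm AE analysis named beside description is a test of no difference at 2-sided .05, and that test cannot support a hypothesis of acceptable safety. The weakness matters most for uncommon events, such as individual Tuina reactions or SAEs if these prove rare. With a control rate of 5% or below, the test would miss a doubling in about 69% to 94% of trials of this size. For a common endpoint it would usually detect one.

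These figures rest on assumed event rates, a doubling of risk, 115 per arm and uncorrected chi-square or Fisher tests. They show how far the test depends on the unknown rate and are not a property of the plan. The primary efficacy analysis is unaffected.

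**What to change.** In Outcome Analysis, make estimation the basis of the safety statement:
- Report the between-arm risk difference with a 95% CI (Newcombe or exact) for participants with at least 1 AE, at least 1 treatment-related AE and at least 1 SAE.
- Give the exact upper limit of the 2-sided 95% CI for each named Tuina reaction and for SAEs in the Tuina arm.
- State that safety statements rest on these intervals and that P>.05 is not evidence of safety.
- Bring the wording in Principal Findings and in Future Directions and Dissemination into line with this.

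The cost is a few sentences, with no new data, visits or participants. The downside is that intervals for rare events will be wide, so the safety statement becomes less favourable than a bare report of no significant difference.
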